### Outcome measures

As previously reported, infants will be assessed according to the timeline (Fig. 1). The primary outcome measure, assessing the motor development, will be the IMP. The selected secondary outcomes will be the: PDMS-2, BSID-III Cognitive subscale, standardized video-recordings of parent-infant interaction, Teller Acuity Cards® and Actigraphic analysis (Motionlogger Microwatch). Due to multiple outcomes and variable willingness of infants, each evaluation time would be completed, if necessary, in two successive days to guarantee greater compliance.

### Primary outcome measure

#### Infant motor profile (IMP)

IMP is a video-recorded motor evaluation of the infant placed in different positions (supine, prone, sitting, standing while grasping and manipulating objects). It is composed at first by observation of spontaneous activity and then by stimulation of motor abilities and manipulation of objects in different position. It consists of 80 items, subdivided in five motor domains, which allow for a calculation of a total IMP score. IMP does not only evaluate motor performance in quantitative terms, but also provides qualitative assessments, such as movement variability and fluency and adaptability of motor strategies.

It is suitable for infant born at term and preterm from 3 months of age to until the child has acquired good autonomous skills (which is approximately 18 months).

Previous studies with CT have had the IMP as the primary outcome measure. It will be carried out at all assessments as shown in Fig. 1.

### Secondary outcome measures

According to secondary goals, the following measures have been selected.

### Motor assessment

#### Peabody developmental motor scales - second edition (PDMS-2)

It evaluates fine and gross motor movements from birth to 5 years. The scale is made up of 6 subtests (reflex, sitting, walking, manipulation of objects, grasping and visual-motor integration), whose results are combined into 3 global motor performance quotients: Gross Motor, Fine Motor and Global Motor [32]. It will be performed at all time-points (T0, T1, T2 and T3).

### Cognitive assessment

#### BSID-III-cognitive subscale

It is a standardized scale for the cognitive development assessment in 1–42 months old children [33]. It will be performed at T0 and T3.

### Visual function assessment

#### Teller acuity cards®

It is a test widely used in young infants and non-collaborative subjects to estimate visual acuity. The trained assessor proposes a series of black and white stripes cards with different widths on one side and neutral stimulus (grey background) on the other side to the infants, judging his/her visual attention. It evaluates the skill to look at a visual target. The estimated visual acuity is the thinnest width of stripes that the child is able to fix and prefer to the neutral grey area. The test is based on the “preferential looking” concept; response indicators are on a spontaneous behaviour basis, i.e. head positioning and eye directing to stimulus. The test is highly reliable, versatile, and it can be executed in a few minutes [34, 35]. It has been used in scientific studies for evaluating the results of training on visual development [36]. It will be performed at T0, T1, T2 and T3. A further complementary visual assessment will be carried out by means of an eye-tracker (CareToy C) [37] that allows a measurement of fixation and pursuit.

### Parent-infant relationship assessment

#### Standardized video-recordings of parent-infant interaction

A video of a free play interaction of about 3–5 min between parent and child will be carried out. Videos will be classified by expert certified raters according to Child – Adult Relationship Experimental Index (CARE – Index) [38] and/or Emotional Availability (EA) Scales [39], blinded to allocation group. They will be carried out at T0, T1, T2 and T3.

### Study of organization and maturity of sleeping

#### Movement recording with Actigraphs

Actigraphs is the simplest and least invasive measurement tool to evaluate sleep which allows for protracted monitoring (from days to months) [40]. It uses accelerometric sensors similar to a wristwatch and it is generally worn on the non-dominant side (hand or wrist). Motionlogger Microwatch will be used and combined with Sadeh algorithm for sleep evaluation. Clinical data such as total sleep time (TST), waking after sleep onset (WASO), and sleep efficiency (SE) will be calculated during the training. It will be worn on an infant’s ankle for 1 week at T0 and T1.

### Questionnaires

#### BSID-III social-emotional scale

This is a subscale of the Bayley III. It is a screening tool for early identification of social-emotional deficits in subjects from birth to 42 months. It is a questionnaire to be completed by parents and it allows an evaluation of child emotional-functionality, communicative needs, interactive relationship and use of interactive emotions to social problem-solving [41]. This scale will be done by the parents at T0, T1, T2 and T3.

#### Parenting stress index (PSI)

This questionnaire, containing 36 items, is divided into 3 subscales and requires about 5–10 min to fill out. It detects defined features of parents, of their children and of their environment that are frequently related to parenting stress. It is a tool, widely used for early detection of parent-child dysfunction in their relationships [42]. It will be filled in by the parents at T0, T1, T2 and T3.

### Analyses

Statistical Package for Social Sciences (SPSS) will be adopted for carrying out the statistical analyses. Descriptive statistics will be performed to create the record of the data for each group. Potential baseline differences and between group differences will be explored computing the *p* values. When necessary, Bonferroni correction will be applied. Firstly, delta changes immediately after treatment (T1, primary endpoint) vs baseline will be calculated to assess the short-term effects of CT-R training versus IM in primary and secondary outcome measures, taking account as covariates base level of motor development, type and grading of brain lesion, family compliance and dose of intervention. After, multivariate statistics will be performed.

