### Study design

To make a comparison between the effects of CT training and IM in brain-damaged infants, a multicentre, evaluator-blinded, paired RCT will be carried out.

The involved clinical centres are the Department of Developmental Neuroscience, IRCCS Fondazione Stella Maris in Pisa; the Neonatal Intensive Care Unit of University Hospital “Santa Chiara” in Pisa, the Neonatal Intensive Care Unit, Department of Perinatal Medicine of University Children’s Hospital “A. Meyer” and the Division of Neonatology, Careggi University Hospital, in Florence.

There will be two investigative arms: CT-R and IM training. Both training programs will last 8-week.

All the infants will be clinically assessed at T0 (baseline, in the week preceding CT-R training/IM) and at T1 (i.e. in the week after the end of the 8-week programme of CT-R training/IM). T1 will be the primary endpoint. Then, all infants will be followed at T2 (i.e. 8 weeks after the end of intervention period) and at T3 (i.e. at 18 months of age). Figure 1 shows the detailed timeline.

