### Sample size

Based on the chosen primary outcome measure, Infant Motor Profile (IMP [31],), and on IMP results of a pilot study and of previously conducted RCT in preterm infants without congenital brain lesions [15, 19, 20] and considering a 80% power and a significant level of 0.05 and a effect size of at least 0.6, a sample of 38 children is required. However, considering also a 10% of drop-out rate, a minimum of 42 infants will be required. In order to facilitate parental work and participation in the project, eligible twins will be allocated into the same group.

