### Randomisation

Randomization will be done after enrolment: participants will be randomly assigned to CT-R training or IM group by the use of an automatic generation of 1:1 sets. A third party blind to clinical aspects of trial will manage these sets, sealing them in numbered envelopes.

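### Where the plan corrects across several outcomes, Holm's step-down procedure would do Bonferroni's job at the same 5% and never reject less: a cheap improvement, not an error

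*Protocol article*

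**What the plan says.** The Analyses section first describes the comparisons: "Potential baseline differences and between group differences will be explored computing the *p* values". The next sentence is the whole of the multiplicity plan: "When necessary, Bonferroni correction will be applied". No family, number of tests or adjusted significance level is given. The section then turns to changes from baseline to T1, compared between arms for the primary and secondary measures.

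There is one primary outcome, the IMP, with T1 as the primary endpoint. The secondary list opens: "The selected secondary outcomes will be the: PDMS-2, BSID-III Cognitive subscale, standardized video-recordings of parent-infant interaction". It continues with the Teller cards and actigraphy. Two parent questionnaires, the BSID-III social-emotional scale and the PSI, are described later in the outcome sections.

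The Sample size section plans on the IMP alone, "considering a 80% power and a significant level of 0.05 and a effect size of at least 0.6", and concludes that "a sample of 38 children is required". No power is claimed for any secondary outcome.

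**The concern.** Bonferroni tests each of m outcomes at 0.05/m. Holm tests the smallest p value at 0.05/m, the next at 0.05/(m-1), and so on, and stops at the first failure. Both control the family-wise error at 5% under any dependence between the outcomes, and Holm can only add rejections. Naming plain Bonferroni therefore gives up some power.

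The secondary aims cover quality and quantity of motor development, vision, parent-infant interaction and sleep. They would be judged in about 38 infants, a number set for the primary outcome only. Power for the secondary outcomes is scarce, so it is worth asking how much the choice of correction costs.

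**Working it through.** **The plan's own figures.** There is no adjusted significance level or number of tests to reproduce. The usable inputs are:
- 38 evaluable infants. With dropout, "considering also a 10% of drop-out rate, a minimum of 42 infants will be required"; 38 × 1.10 = 41.8, rounded up to 42.
- Allocation by "automatic generation of 1:1 sets", so 38/2 = 19 per arm.
- Significance level 0.05. The protocol does not state sidedness; two-sided is assumed here.
- Effect 0.6, stated for the IMP and borrowed here for the secondary outcomes.

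**Family size (assumption).** Six secondary measures are scheduled at both T0 and T1: PDMS-2, Teller cards, parent-infant video, actigraphy, BSID-III social-emotional and PSI. BSID-III Cognitive is taken at T0 and T3 only, so it has no T1 value. Hence m = 6, with one test per measure. Counting PDMS-2 quotients, sleep variables or PSI subscales separately would give a larger m.

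**Thresholds for m = 6.**
- Bonferroni: 0.05/6 = 0.0083 for every outcome.
- Holm, in order of the p values: 0.05/6 = 0.0083, 0.05/5 = 0.0100, 0.05/4 = 0.0125, 0.05/3 = 0.0167, 0.05/2 = 0.0250, 0.05/1 = 0.0500.

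The first step is the same in both. So for a given family the chance of at least one rejection is identical, and the gain lies only in how many further outcomes are declared.

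**Bonferroni power per outcome, exact.** For a two-sample t test with 19 per arm there are 36 degrees of freedom. The two-sided critical value at 0.0083 is 2.792, and the noncentrality is d × √(19/2).
- d = 0.6: noncentrality 1.849, power 19.0%
- d = 0.8: noncentrality 2.466, power 38.6%
- d = 1.0: noncentrality 3.082, power 61.6%

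**Bonferroni against Holm, simulated.** Six normal outcomes with pairwise correlation 0.3 (assumed), 19 per arm, unadjusted two-sided t tests, 100,000 trials per row:

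| Real effects | Size (SD) | Average power, Bonferroni | Average power, Holm | At least one rejection (both) | Error among true nulls, Bonferroni / Holm |
|---|---|---|---|---|---|
| 0 of 6 | 0 | – | – | 4.7% | 4.7% / 4.7% |
| 3 of 6 | 0.6 | 18.9% | 20.0% | 42.8% | 2.4% / 2.8% |
| 6 of 6 | 0.6 | 19.0% | 22.6% | 59.5% | – |
| 3 of 6 | 0.8 | 38.5% | 41.0% | 70.3% | 2.5% / 3.4% |
| 6 of 6 | 0.8 | 38.6% | 47.5% | 85.1% | – |
| 6 of 6 | 1.0 | 61.6% | 74.1% | 96.9% | – |

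The simulated Bonferroni column agrees with the exact values. In no trial did Bonferroni reject an outcome that Holm did not. With all six effects real, Holm declared at least one further outcome in about 15% of trials at 0.6 SD and 35% at 0.8 SD.

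**Sensitivity to m and correlation** (d = 0.6, normal approximation, correlation 0 and 0.5):
- m = 5: 23.4% to 24.0–24.3% with two real effects; 23.4% to 26.6–28.4% with all real.
- m = 7: 20.0% to 20.4–20.5% with two real effects; 20.0% to 22.4–24.6% with all real.

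The gain is under 1 point with two real effects and about 2 to 5 points with all real.

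**The case against.** The strongest reply is that this is a preference. Bonferroni is an accepted method that controls the family-wise error, contradicts nothing else in the protocol, and leaves the single primary outcome and its sample size untouched. No power target for a secondary outcome is missed, because none is stated. All of this stands, and it is why the point is an improvement and not an error.

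A reader might go further and infer that the trial will lose secondary findings for nothing. The document does not support that, for four reasons.
- The correction is not tied to the secondary outcomes. It follows a sentence covering both baseline and between-group comparisons, and it applies only when judged necessary. With one primary outcome at one primary time point, the secondary outcomes are the natural place for it, but that is an inference. A full analysis plan, not shown, may define the family.
- The family of six is a construction. The Outcome measures section lists five secondary outcomes, one of them without a T1 value; six is reached by adding the two questionnaires.
- The larger gains need every outcome to carry an effect of 0.8 to 1.0 SD against an active comparator. The only planning effect in the document is 0.6.
- Bonferroni gives something back: simple matching simultaneous intervals, and a slightly lower actual error when some nulls are true (2.5% against 3.4% with three effects of 0.8). The interval advantage is minor here, since the Analyses section mentions only p values.

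The simulation uses unadjusted independent-groups tests, whereas the plan adjusts for covariates and describes a "multicentre, evaluator-blinded, paired RCT will be carried out". That would change the power levels, but not the fact that Holm never rejects less.

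**Conclusion.** The point holds as a low-cost efficiency suggestion. That Holm rejects at least as much as Bonferroni at the same family-wise 5% rests on no assumption about this trial. The size of the gain does: with six outcomes, 19 per arm and correlation 0.3, it is about 1 point of average power at 0.6 SD if three effects are real and about 4 points if all six are. At 0.8 and 1.0 SD with all six real it is 9 and 12 points. The chance of any secondary finding, the primary analysis and the sample size are unaffected.

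**What to change.** In the Analyses section, replace the Bonferroni sentence with wording such as: *The T1 between-group tests of the secondary outcomes measured at T0 and T1 form one family and are tested with Holm's step-down (Holm-Bonferroni) procedure at family-wise 5%; the IMP at T1 is tested alone at 5%.* This also names the family, which the present sentence leaves open.

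The cost is one sentence and no further infants. Holm has no simple matching simultaneous confidence intervals, so ordinary 95% intervals would be shown and labelled as unadjusted. The actual error among true nulls rises slightly but stays below 5%.

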### Study sample and recruitment

Participants will be recruited at Tuscany Neonatology Units in Pisa (Santa Chiara University Hospital) and in Florence (Meyer and Careggi Hospitals). The neonatological staff will assess eligibility of infants on the basis of inclusion and exclusion criteria prior to hospital discharge and staff will inform parents about study. If a family expresses interested in participating in the study, they will receive an introductory letter and an informative flyer. Recruitment must take place within the first year of age of the infant and, because of the characteristics of the interventional setting and exercises, before the complete acquisition of the trunk control in sitting position. If parents are willing to participate, they will be asked to sign a first agreement for admission to the observation phase and another one to partake in the intervention phase. As indicated above, Tuscan Region Paediatric Ethics Committee approved the clinical trial. Moreover, CT-R, as the previous CT, has been classified as a medical device without an EC mark, so an approval of a new clinical trial was requested and obtained by the Italian Ministry of Health.

Inclusion criteria will be the following:Abnormal or specific neurological signs at neurological examination of GMA or HINE, associated with one of the following conditionsPersistent brain ultrasound periventricular hyper-sonorityEvidence of cerebral haemorrhageEvidence of Periventricular Leukomalacia (PVL)Cerebral strokeModerate or severe asphyxia

Exclusion Criteria:Polymalformative syndrome or cerebral malformationsSevere retinopathy (III-IV degree)Severe sensory disturbances (deafness or blindness)

Moreover, to be enrolled in the intervention phase, additional inclusion criteria will be:Persistence of abnormal Spontaneous GMs evaluation according to Prechtl at 2–3 months post-term (absent or abnormal FMs)Persistence of abnormal/specific signs according to HINE

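### The single covariate list for the T1–T0 changes omits age at T0 and the non-motor outcomes' own T0 values, which loses precision

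*Protocol article*

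**What the plan says.** The Analyses section states that "delta changes immediately after treatment (T1, primary endpoint) vs baseline will be calculated" in order to assess the "short-term effects of CT-R training versus IM in primary and secondary outcome measures". It attaches one covariate list to all of these changes: "taking account as covariates base level of motor development, type and grading of brain lesion", and the list runs on, "type and grading of brain lesion, family compliance and dose of intervention". Baseline motor level is not tied to an instrument, and age does not appear.

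Under Outcome measures the article says: "The primary outcome measure, assessing the motor development, will be the IMP". The non-motor outcomes recorded at both T0 and T1 are Teller acuity, the parent-infant interaction videos, actigraphy, the Bayley Social-Emotional scale and the Parenting Stress Index (PSI). For the PSI, for example: "It will be filled in by the parents at T0, T1, T2 and T3". The Bayley Cognitive subscale is scheduled at T0 and T3 only, so it has no T1 change.

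On age, Study sample and recruitment says: "Recruitment must take place within the first year of age of the infant". The Ages & Stages score bands for starting treatment cover 3–4, 5–6 and 7–8 months. Infants without head control may wait for it within the first year.

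**The concern.** A change score adjusted for a different baseline variable behaves much like an unadjusted change score. It subtracts the whole of the T0 value, although the T1 value usually depends on only part of it, so noise in the T0 measurement passes into the treatment contrast. Baseline motor level is a weak substitute for baseline parenting stress, sleep or visual acuity.

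Age raises a similar issue. Entry is confined to a motor window, from first head control to before independent sitting, so the range of motor level is restricted while age may differ by several months. Two infants at the same motor level and different ages need not be on the same path, and motor scores, acuity and sleep can all be expected to change with age in infancy. The Randomisation section describes no stratification by age. The Sample size section places twins, who share an age, in the same arm, which makes an age difference between arms somewhat more likely.

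At stake is avoidable variance, and estimates that move with chance baseline differences, in a trial with about 19 evaluable infants per arm.

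**Working it through.** **Inputs.** 38 evaluable and 42 enrolled (Sample size); 1:1 allocation (Randomisation). The article gives neither the T0–T1 correlation r nor the share of residual variance explained by age. I assume r from 0.3 to 0.9 and an age share R² from 0.05 to 0.30.

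**1. The plan's own figure.** 38 × 1.1 = 41.8, which rounds up to 42. The 38 is matched by a one-sided paired t-test at effect size 0.6 (19 pairs, power 80.8%); the article says paired but does not say one-sided. I use it here only as the number analysed: 38 / 2 = 19 per arm.

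**2. Precision lost without the own T0 value.** Scale the outcome to SD 1 at both visits. Per infant, the variance of the change is 2(1 − r), and the residual variance after adjusting for own T0 is 1 − r². The ratio is (1 − r²) / [2(1 − r)] = (1 + r)/2.

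| r (assumed) | change | own-T0 adjusted | ratio | reduction |
|---|---|---|---|---|
| 0.3 | 1.40 | 0.91 | 0.65 | 35% |
| 0.5 | 1.00 | 0.75 | 0.75 | 25% |
| 0.7 | 0.60 | 0.51 | 0.85 | 15% |
| 0.9 | 0.20 | 0.19 | 0.95 | 5% |

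**3. Does the motor covariate already recover this?** In 20,000 simulated trials (19 per arm, no true effect, r = 0.5, motor level correlated 0.3 with the outcome at both visits), both models contained motor level.
- Without own T0, the mean estimate was −0.002 and its SD 0.327.
- With own T0, the mean was −0.001 and the SD 0.283.
- The variance ratio was 0.75, so motor level did not stand in for the missing baseline. Both means are essentially zero, so neither model is biased.

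**4. Chance imbalance.**
- The SE of the T0 difference between arms is √(2/19) = 0.324 SD.
- P(|difference| ≥ 0.5 SD) = P(|Z| ≥ 0.5/0.324 = 1.54) = 0.12 for each outcome.
- The shift in the change-score contrast is (1 − r) × imbalance. At r = 0.5 it is 0.5 × 0.324 = 0.16 SD for a typical imbalance and 0.5 × 0.5 = 0.25 SD for one of 0.5 SD. The simulated slope was −0.49 per SD, which agrees.
- This shift is not an extra cost on top of step 2. The variance gap in step 3 is 0.327² − 0.283² = 0.107 − 0.080 = 0.027, and the imbalance term 0.49² × 0.324² = 0.025 accounts for nearly all of it.

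**5. Age.** If age at T0 explains a share R² of the variance left after the other covariates, adjusting for it is equivalent to multiplying the sample by 1/(1 − R²). That is 1.05 at 0.05, 1.11 at 0.10, 1.25 at 0.20 and 1.43 at 0.30.

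**The case against.** The strongest reply concerns the primary outcome. The Infant Motor Profile (IMP) is described as the measure of motor development, so the motor covariate most naturally means its T0 score. Regressing the change on arm and own T0 gives the same arm estimate as regressing T1 on arm and own T0, so on that reading the primary outcome is already handled as it should be. The PDMS-2 is also motor and is largely covered. This stands. A reader might infer that every outcome lacks its own baseline, but the article does not support that; for the IMP, what remains is that the instrument is not named and age is absent.

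A reader might also infer regression-to-the-mean bias. Allocation is randomised, so the change-score contrast is unbiased on average, as the simulation shows. Only a shift conditional on chance imbalance remains. Nor is motor level the only covariate: lesion type and grading, compliance and dose are listed too. An entry range of 3 to 12 months is not stated either; the article gives the first year as the limit and score bands from 3 to 8 months.

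Two further objections stand in part. Neither r nor the age R² is documented, so the size of the gain is a range. The article is condensed, and a fuller plan may give a separate model for each outcome. However, the article does not leave the covariates open: it names one list and applies it to primary and secondary outcomes alike. The design is called paired, but no pairing variable is given, so control of age by design cannot be assumed.

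**Conclusion.** The point holds as one of precision. As written, five non-motor secondary outcomes are analysed as changes without their own T0 value, and no outcome is adjusted for age at T0. For those five, own-baseline adjustment would reduce variance by 5% to 35% for an assumed r of 0.9 to 0.3, taking equal SDs at the two visits. The gain from age would be about 5% to 43% more effective infants for an assumed R² of 0.05 to 0.30. At the low end of both ranges the gain is small.

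With 19 per arm, a baseline imbalance of 0.5 SD or more has about a 12% chance for any one outcome and would move its estimate by 0.25 SD at r = 0.5. This is exposure to chance, not systematic bias. The own-baseline figures do not apply to the IMP if the motor covariate is its T0 score, or to the Bayley Cognitive subscale, which has no T1 value. The change is worth making because it is nearly free, but the omission does not invalidate the planned comparison.

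**What to change.** For each outcome with T0 and T1 values, model the T1 value (or the change) on arm, that outcome's own T0 value, corrected age at T0 and the lesion covariate. For the primary outcome, state that the baseline motor covariate is the T0 IMP score; for the PDMS-2, use its own T0 score. Family compliance and dose arise after randomisation. Whether they belong in the model is a separate question, and this point does not depend on it.

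The cost is a change of analysis wording and one or two degrees of freedom per model. The T0 scores are already scheduled, and age is already needed to apply the start-of-treatment score bands, so no new data are required.
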